### Subject withdrawal/exclusion

In accordance with the Declaration of Helsinki, the participant can discontinue their involvement in the study at any point if either they or their parent/guardian wishes to be withdrawn from the study.

Participants may be excluded from the study if they exhibit a condition that contradicts the initial criteria or if, at any stage, they are deemed unfit to continue the study at the investigator’s discretion. Any decision to withdraw will be documented in the source records and the relevant CRF. Subsequently, individuals who choose to withdraw from the study will be substituted. Samples from those who opt to no longer participate in the study will be preserved and may undergo analysis within the research. Furthermore, participants who are excluded from the study after giving their consent will also be replaced.

### Sample collection and analysis

#### Sample collection

##### Stool and urine

Stool and urine samples will be collected by the participant (or parent/guardian depending on the age of the participant) in the hospital using a collection kit and instructions that will be provided. If the samples are required to be collected at home, participants are informed that the samples provided should be as fresh as possible, ideally within 12 hours or less. Index cases and sibling control urine samples are collected in standard Steriline containers. Index cases are instructed to place their stool samples into a standard collection box, while the stool samples of sibling controls are collected anaerobically using the GutAlive anaerobic stool collection kit for culturomics. The GutAlive kit preserves the viability of anaerobic bacteria without altering the overall microbiome composition, ensuring that valid comparisons can be made between index cases and sibling controls despite the slight difference in sample collection methods. This distinction in collection methods was necessary due to the differing objectives of the study for each group; however, both groups follow consistent handling and storage protocols. The stool samples are then placed in an empty biohazard bag. It is then stored at 4°C. Freezer bags are provided to all participants to ensure samples remain cold when being transported to the hospital. A research nurse transfers samples from the participants’ homes to the laboratory if the participants are not scheduled for a hospital appointment close to the time of sample collection.

Once at the laboratory, the stool and urine samples are stored at −80°C for long-term preservation. Stool samples from sibling controls, collected anaerobically using the GutAlive anaerobic stool collection kit, aim to maintain microbial integrity and allow for the culturing of highly sensitive anaerobic bacteria. Anaerobic samples are immediately cultured under anaerobic conditions on arrival to the laboratory, while the remaining stool is stored at −80°C for future analysis. Anaerobic stool samples are serially diluted and plated on five different media (Brain Heart Infusion; De Man, Rogosa and Sharpe; Tryptic Soy Broth; Yeast Casitone Fatty Acids; M17 Medium; Gifu Anaerobic Medium) to target a broad spectrum of taxa.

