### Sample analysis

Stool will be analysed by the APC Microbiome Ireland laboratory. Stool samples will be stored at −80°C. The extraction of DNA from faecal matter will be conducted using the QIAmp Fast DNA Stool Mini Kit (QIAGEN, Manchester, UK), which includes an initial bead-beating step in the process.^68^ Microbiome analysis of stool will be performed using shotgun metagenomics sequencing. Initially, the DNA will undergo fragmentation, where it is sheared into fragments of approximately 400–600 bp and tagged with Illumina adaptor sequences. Subsequently, an indexing PCR will be carried out to uniquely index each sample, facilitating the pooling of samples on a single-flow cell and subsequent bioinformatic demultiplexing. Following Illumina Nextera XT protocols, PCR amplicons will be cleaned and normalised. To ensure an even distribution of samples for pooling, qPCR will be conducted. All metagenomic samples will be sequenced on the Illumina NextSeq platform. Raw reads will be filtered based on quality, quantity and length of reads, as well as the removal of human reads. Stool microbiota composition and functionality will be analysed using state-of-the-art methods. Faecal SCFAs will be measured in all study participants as SCFAs have previously been reported to have a protective effect against developing autoimmunity.^69^,^72^ Faecal SCFAs will be analysed by gas chromatography flame ionisation detection using a Varian 3800 GC system, fitted with a DB-FFAP column (30 m L × 0.32 mm ID × 0.25 µm df; Agilent, California, USA) and a flame ionisation detector. Urine for metabolomics will be stored at −80°C and later analysed for untargeted metabolomics at University College Cork. Mass spectrometry methods for biomarker identification, followed by targeted/hypothesis-driven metabolomics methods for biomarker verification, will be conducted.

Statistical instruments for the analysis of microbiome data sets are continually being updated, and we will use the latest methodology available. Part of the faecal samples will be grown for analyses of culturable bacterial strains.

Serum for diabetes autoantibodies will be analysed by Exeter Clinical Laboratory in the UK. Serum for HLA-typing will be analysed at the National Blood Centre, [name]. Serum for HbA1C measurement, glucose and C peptide analysis will be analysed at CUH. Samples will be stored securely in a UCC monitored biobank until transfer for analytics to the relevant laboratory.

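### Cases and sibling controls use different stool collection devices, so a case–sibling difference in stool levels at any visit cannot be separated from a device effect

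*Protocol article*

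**What the plan says.** All of the following is in the protocol article.

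- **Devices (Stool and urine).** "Index cases are instructed to place their stool samples into a standard collection box, while the stool samples of sibling controls are collected anaerobically", the latter with the GutAlive kit. The opening of Methods and analysis gives the reason: only sibling stool is cultured, to build a biobank.
- **The article's defence (same section).** "The GutAlive kit preserves the viability of anaerobic bacteria without altering the overall microbiome composition, ensuring that valid comparisons can be made". It adds that "both groups follow consistent handling and storage protocols".
- **A control-only laboratory step (same section).** "Anaerobic samples are immediately cultured under anaerobic conditions on arrival to the laboratory"; what is left of that stool is then frozen at −80°C.
- **What is measured (Sample analysis, Microbiome analysis).** Shotgun sequencing with species, functional and strain profiling. In addition, "Faecal SCFAs will be measured in all study participants".
- **What is compared (Objectives and outcomes).** The primary aim is to describe how the microbiome and metabolome evolve in the first year of stage 3 type 1 diabetes (T1D), relative to siblings without diabetes. The strengths list says the sibling comparison will help to find biomarkers at disease onset.
- **Size and timing (Methods and analysis).** 50 cases and 50 sibling controls, with stool at 0, 4, 8 and 52 weeks.

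**The concern.** A case–sibling comparison of stool levels has a clear meaning only if the two groups' samples differ in disease status and not in how they were obtained. Here every case sample comes from one device and every control sample from the other, at all four visits. The control device was chosen because it treats anaerobic organisms differently.

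The article recognises the issue and answers it by assertion, but the assertion is narrower than the use made of it. It speaks of overall composition, whereas the study looks for specific microbial biomarkers and profiles species, strains and functions. It does not mention SCFAs, which are metabolites rather than part of composition. It also describes the kit alone, whereas a valid comparison needs the two devices to agree with each other.

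At stake is the level comparison with siblings, in particular the difference at diagnosis. A device effect that recurs at each visit would look like a stable disease signature.

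**Working it through.** The article states no power, effect size or device-effect figure, so there is nothing to reproduce. Three checks apply.

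**1. Can any model separate device from disease?** Inputs from the article: 50 cases, 50 controls, 4 visits, one device per group. Rank of the design matrix:

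| Model | Columns | Rank |
|---|---|---|
| Visit + group | 5 | 5 |
| Visit + group + device | 6 | 5 |
| Visit × group | 8 | 8 |
| Visit × group + device + device × visit | 12 | 8 |

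Adding device never adds rank, so the device term cannot be estimated alongside group. An analysis plan cannot repair this.

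**2. Which contrasts are affected?** Let δ_t be the disease effect at visit t and κ_t the shift caused by using the anaerobic kit instead of the box, on the analysis scale.

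- Level contrast, case minus control at visit t: δ_t − κ_t. The shift remains.
- Change contrast from baseline: (δ_t − δ_0) − (κ_t − κ_0). If κ is constant over visits, it cancels.

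The article neither states nor tests that κ is constant. It could vary, for example, with hospital versus home collection. The change contrast also cannot show a difference that is already present at diagnosis and stays stable.

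**3. How sensitive is a level comparison?** Assumptions, none from the article except n = 50 per group: independent groups, a feature scaled to SD 1, no true disease effect, a two-sided unadjusted 5% test, and a device shift of d SD.

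SE = √(2/50) = 0.20. Rejection probability = Φ(d/SE − 1.96) + Φ(−d/SE − 1.96).

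| d (SD) | d/SE | Rejection probability for that feature, one visit |
|---|---|---|
| 0 | 0 | 5% |
| 0.2 | 1.0 | 17% |
| 0.3 | 1.5 | 32% |
| 0.5 | 2.5 | 71% |

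For scale, the true difference detectable with 80% power is (1.96 + 0.84) × 0.20 = 0.56 SD. A device shift within this assumed range would therefore be comparable in size to the disease effects the study could detect.

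**The case against.** The strongest reply is that the article anticipates the problem, states that the kit is neutral, and may have validation data in the full protocol or laboratory manual, which are not shown. Sequencing also measures DNA, and loss of viability is not loss of DNA. This has force: the documents do not show that a device effect exists. But the published assurance covers overall composition only, and it does not extend to individual taxa, function or SCFAs.

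Some stronger readings are tempting but are not supported.

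- **That every case–control result is affected.** Change contrasts are protected under a constant additive effect, and evolution over the year is part of the primary aim. Urine uses the same container in both groups. The objectives on diabetic ketoacidosis (DKA) and its severity, glycaemic control, beta cell reserve and preceding hyperglycaemia concern cases, who all use one device.
- **That the bias favours the hypothesis of depleted species in T1D.** It could, but nothing in the documents fixes a direction.
- **That the handling claim is plainly contradicted.** The control-only culture step sits awkwardly with it. However, both groups share cold storage, cold transport and −80°C freezing, and the culture step can be read as aliquoting in parallel without delay.
- **That samples wait up to 12 hours.** Twelve hours is an ideal for home collection, neither a cap nor the usual route.
- **That 17%, 32% or 71% of features would be false positives.** These are probabilities for one feature given an assumed shift. They would be shares of features only if every feature shifted by that amount.

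**Conclusion.** The concern holds for case–sibling differences in stool levels at a visit: taxa, functional profiles and SCFAs. For these, aliasing of device with disease is complete and follows directly from the collection procedure. The statement that comparisons are valid is not supported as written.

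The consequence is less certain than the aliasing. The figures of 17%, 32% and 71% rest on assumed shifts and an unadjusted test. They show sensitivity and are not evidence that bias is present. A multiplicity correction would lower the rates but leave the bias in the estimates.

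This should be fixed because it touches the primary comparison, analysis cannot correct it, and the remedy for remaining samples is cheap.

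**What to change.** 1. **Split control stool at all remaining visits.** One portion goes into the same standard box as cases, is frozen in the same way, and is used for sequencing and SCFAs. The rest goes into the anaerobic kit for culturomics. This removes the confounding for those samples.
2. **Bridge to control samples already collected.** At remaining visits, analyse both portions from about 20 controls, estimate the device shift for each feature, and flag strongly device-sensitive features. With within-stool correlation r, the 95% half-width is 1.96 × √(2(1 − r)) / √20. Assumed r = 0.7, 0.8 and 0.9 gives ±0.34, ±0.28 and ±0.20 SD. This detects large shifts; it cannot prove equivalence or clear a feature of a 0.2 SD shift.
3. **For samples without a matched device, make group-by-time change contrasts the main case–sibling inference**, with the constant-effect assumption stated. Each control's change must be taken within one device. A kit sample at baseline and a box sample later would bring the device effect back, so controls who straddle the switch are the natural choice for the paired samples.
4. **Replace the sentence claiming valid comparisons with a stated limitation**, unless the bridging data support it.

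**Cost:** one extra standard box per control visit, a line in the collection instructions, and about 20 duplicate sequencing and SCFA runs, with more if additional controls straddle the switch. The study started in October 2023 with one year of recruitment planned. If few control visits remain, splitting will help little, and bridging may need fresh stool from controls who have finished sampling.

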##### Serum for diabetes autoantibodies

Serum will be collected from controls at study visit 4 to look for the presence of diabetes autoantibodies. This test will have been carried out in all cases, as per standard medical practice when first diagnosed with T1D.

##### Serum for HbA1C

A blood sample will be collected from controls to measure their HbA1C at study visit 4.

##### Serum for HLA-typing

Approximately 5 mL of serum will be collected from cases and controls at study visit 4.

##### Mixed meal tolerance test

Cases will be asked to participate in a MMTT at study visit 4 at CUH. They will be asked to fast from 22:00 the night before the test but continue to take their normal long-acting insulin, including on the morning of the test. Cases on an insulin pump can continue to take their normal background (basal) insulin before, during and after the test.

To proceed with the test, the case’s glucose level must be between 4 and 11.1 mM before the beginning of the test. Serum for HLA-testing will be taken from the intravenous line during the test.

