### Objectives and outcomes

The primary aim of this study is to describe the evolution of the microbiome and metabolome in children during their first year with stage 3 T1D, compared with their siblings without diabetes.

Secondary objectives and outcomes:

To establish if there are differences in the microbiome or metabolome of children who present in diabetic ketoacidosis (DKA) versus those who present without DKA.To establish if there are differences in the microbiome or metabolome in those presenting with mild, moderate or severe DKA.To establish if there is an association between the microbiome or metabolome and glycaemic control during the first year of diagnosis.To establish if there is an association between the microbiome or metabolome and beta cell reserve 1 year after T1D diagnosis.To establish if there is an association between the microbiome or metabolome at the time of T1D diagnosis and preceding hyperglycaemia.

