## Methods and analysis

This study will recruit 50 children at the time of diagnosis and 50 unaffected sibling controls and will employ a prospective cohort study methodology to investigate the faecal microbiome of children with newly diagnosed T1D in the first year of diagnosis. All children with newly diagnosed T1D will be assessed for eligibility for enrolment in this study. Inclusion and exclusion criteria are outlined separately in the recruitment strategy outline. Parents of eligible cases and controls will be approached for consent. If a case does not have siblings, they will still be eligible for recruitment. If a case has multiple siblings, more than one sibling can be recruited as a control. Recruitment will be conducted over a 1-year period. Consent for enrolment for both cases and controls will be obtained during the first hospital visit on diagnosis of the index case. The study started in October 2023 and is planned to finish by September 2026.

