At each time point (0, 4, 8, 52 weeks), stool will be collected for microbiome analysis from all cases and controls (n=100). Urine for metabolomics will be collected from all study participants at the same time points. A food frequency questionnaire will be completed by all cases and controls at the first and fourth study visits (0 and 52 weeks, respectively). Clinical data, including insulin dosing, glycaemic control and blood results, will be documented at each visit for cases. Cases will be asked to participate in a mixed meal tolerance test (MMTT) at study visit four (52 weeks). This will quantify stimulated C peptide. This result will help to establish if there is a correlation between microbiome and metabolome evolution and beta cell reserve at 1 year. Shotgun metagenome sequencing will be conducted on faecal samples and urine metabolomic analysis will be employed to detect metabolic biomarkers. The study will explore the impact of the underlying diagnosis and environmental factors. The mode of delivery plays a crucial role in shaping the composition and function of the neonatal microbiome.^66 67^ Caesarean section delivery affects early microbiota transmission from mother to infant and the subsequent priming of the immune system, with delivery-dependent differences early in gut microbiota colonisation continuing through the first year of life.^66 67^ Due to this, we will record the mode of delivery in our data collection with ethical approval to access patient charts and will perform shotgun sequencing to compare cases with age-matched controls from 6 months onwards, should any become available.

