The second and third study visits will take place when the participant (case) returns to CUH for their routine follow-up appointment with the Diabetes Team approximately 1 and 2 months after T1D diagnosis. At these visits, cases and controls will be asked to provide stool and urine samples to the study team. Clinical data, including insulin dosing and glycaemic control, will be documented. Cases will be examined and height and weight recorded.

### Study visit 4

The fourth study visit will take place approximately 12 months after T1D diagnosis. At this visit, cases and controls will be asked to provide stool and urine samples to the study team. They will also be asked to complete a food frequency questionnaire. Clinical data, including insulin dosing, glycaemic control and blood results, will be documented. Height and weight will be recorded for all study participants. Cases will undergo their MMTT at this visit. If the case opts out of the 2-hour MMTT, they can have a shortened test where a single blood draw is taken at 90 min. If the case does not wish to take part in any MMTT, the results of routine clinical bloods, including fasting glucose and fasting C peptide levels, will be recorded instead. This will help to establish whether there is a correlation between microbiome and metabolome evolution and beta cell reserve. Serum for HLA-typing will be taken at this visit also.

Controls will undergo phlebotomy for HLA-typing, diabetes autoantibodies and HbA1c analysis at this study visit. Parent(s) will be given these results if requested. There will be flexibility in the timing of phlebotomy for controls enrolled in the study. Their blood can be taken at any stage during the study (between study visit 1 and the end of the study) to ensure it is convenient for the family and the control.

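### Week-52 urine is due at the visit where only cases are scheduled to fast and take a test meal, and its timing is neither fixed nor matched, so the one-year urine metabolome contrast is at risk of confounding

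*Protocol article*

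**What the plan says.** The primary aim appears under Objectives and outcomes: "describe the evolution of the microbiome and metabolome in children during their first year with stage 3 T1D, compared with their siblings without diabetes". On numbers, Methods and analysis states: "This study will recruit 50 children at the time of diagnosis and 50 unaffected sibling controls".

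The same section sets sampling at 0, 4, 8 and 52 weeks: "Urine for metabolomics will be collected from all study participants at the same time points". Sample analysis says that this urine goes to untargeted metabolomics, followed by targeted verification.

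For the 52-week visit, Study visit 4 puts two things together. For both groups: "At this visit, cases and controls will be asked to provide stool and urine samples to the study team". For cases alone: "Cases will undergo their MMTT at this visit". The Mixed meal tolerance test section gives the cases' preparation: "They will be asked to fast from 22:00 the night before the test but continue to take their normal long-acting insulin". It also requires glucose to lie between 4 and 11.1 mM before the test can start.

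Study visit 4 allows two departures from the full test. One is shorter: "If the case opts out of the 2-hour MMTT, they can have a shortened test where a single blood draw is taken at 90 min". The other has no meal: "If the case does not wish to take part in any MMTT, the results of routine clinical bloods, including fasting glucose and fasting C peptide" are then recorded.

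Table 2 and Study visit 4 give siblings height and weight, a food questionnaire, stool, urine and blood for HLA, autoantibodies and HbA1c, with flexible timing for the blood. They list no test meal and no fast. The Stool and urine section makes hospital collection the default, allows home collection where needed, and asks for samples ideally no more than 12 hours old.

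**The concern.** Food state is a feature of the sample. If it differs between groups by design, any metabolite that responds to fasting or feeding can differ between groups without any effect of diabetes. Here the schedule places an overnight fast and a test meal in one group only, and only at week 52.

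Week 52 is also the only urine time point after week 8, so it carries most of what the study can say about evolution over the year. Two comparisons are exposed: cases against siblings at week 52, and week 52 against earlier visits within cases. Cases may also differ among themselves. Some will have fasted and taken the meal. Some may have fasted but been stopped by the glucose requirement. Some will have declined the test and had routine fasting bloods recorded, and the article does not say whether those bloods are drawn at the same visit.

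**Working it through.** The article gives no power or sample-size calculation, so there is no figure to reproduce. The check has three parts.

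**1. The two groups side by side at visit 4**

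| | Cases | Siblings |
|---|---|---|
| Study urine | Yes | Yes |
| Fast from 22:00 | Yes, if having the MMTT | No instruction |
| Test meal | Yes, unless declined or not started | None |
| Order of urine relative to fast and meal | Not stated | Does not arise |

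No fast or test meal is described for either group at weeks 0, 4 and 8.

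**2. Does home collection avoid the problem?**

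The MMTT section refers to insulin on the morning of the test, so a morning visit is implied. Assume arrival between 08:00 and 10:00. A home sample within the 12-hour ideal was then passed no earlier than:

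- arrival 08:00: 20:00, so 2 of the 12 hours precede the fast and 10 fall after it begins;
- arrival 10:00: 22:00, so none of the 12 hours precedes the fast.

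Home collection can avoid the fast, but under the current wording most of the permitted window lies inside it.

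**3. How much could it matter? (illustration only)**

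Inputs from the article: 50 cases and 50 siblings. Assumed, because the article gives none of them: two-sided alpha 0.05; a metabolite with no diabetes effect and unit SD; a shift of *d* SD from the fast or meal in a share *f* of cases and in no siblings; a normal approximation that ignores sibling pairing.

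- Expected spurious difference: *fd*.
- Variance in cases: 1 + *f*(1 − *f*)*d*²; in siblings: 1.
- SE = √[(2 + *f*(1 − *f*)*d*²)/50].
- P(reject) = Φ(*fd*/SE − 1.96) + Φ(−*fd*/SE − 1.96).

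Worked case, *d* = 0.5 and *f* = 0.5: *fd* = 0.25; SE = √[(2 + 0.0625)/50] = 0.203; ratio 1.231; P = Φ(−0.729) + Φ(−3.191) ≈ 0.234.

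Probability of a false positive per null metabolite (nominal 5%):

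| Shift *d* | *f* = 25% | 50% | 75% | 100% |
|---|---|---|---|---|
| 0.3 SD | 6.6% | 11.6% | 20.2% | 32.3% |
| 0.5 SD | 9.5% | 23.4% | 45.8% | 70.5% |
| 0.8 SD | 16.3% | 48.6% | 83.0% | 97.9% |
| 1.0 SD | 22.3% | 65.4% | 94.8% | 99.9% |

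If food state is balanced between groups (*f* = 0 here), the rate returns to 5%. The spurious difference *fd* does not depend on sample size, so recruiting more children would not remove it.

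**The case against.** The strongest reply is that this is a condensed article. Void timing, food state and case report form fields usually sit in a full protocol or sampling procedure, which is not shown, so one cannot claim that they go unrecorded. That part stands. It does not answer the point, because the same-visit pairing of study urine with a case-only fast and meal is stated design, not missing detail. The article also defends comparability where stool is collected differently in the two groups, and offers no such argument for urine.

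A reader might infer that the week-52 contrast is confounded outright, with all 50 cases sampled fasted or after the meal and all siblings fed. The documents do not support that. They do not say that case urine is passed during the fast or after the meal. Home collection is possible. The MMTT can be shortened, declined or not started. For siblings, the absence of a test meal is clear, but on fasting the text is only silent, and a sibling's morning sample could also follow a night without food.

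Three further limits are fair. Faecal short-chain fatty acids are measured in all participants, so urine is not the only source of metabolite data. The composition of the meal is not described, so its effect on urine cannot be judged from the article. The study calls itself exploratory and its primary aim is descriptive; this lowers the cost of an isolated false lead, but a systematic difference in food state would still distort the description.

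**Conclusion.** The concern holds as a risk of confounding, not as demonstrated confounding. The schedule puts a fast and a test meal in cases only, at the only urine time point after week 8, and neither fixes nor matches urine timing around them. Exposed are the week-52 case-sibling urine metabolome contrast, which belongs to the primary aim, and the change in cases from weeks 0-8 to week 52.

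The size is unknown. The range of 6.6% to 99.9% follows entirely from assumed shifts of 0.3 to 1.0 SD in 25% to 100% of cases, with no sibling affected; it shows how sensitive the comparison is and is not an estimate of the bias. Whether analysis could adjust for food state depends on what is recorded and on some overlap between groups, and the article settles neither.

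Weeks 0, 4 and 8 are not affected by the MMTT, although food state is not standardised there either. No claim is made here about the stool microbiome. The point is worth acting on because the remedy is cheap and easier to apply before the week-52 samples are collected than after.

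**What to change.** - **One visit-4 urine condition for both groups.** In Study visit 4 and in the Stool and urine section, specify a single collection condition for cases and siblings that is separate from the MMTT. An example is an evening home sample passed before 22:00 on the day before the visit, kept cold and brought to the morning visit. That is about 12 hours; with a late-morning arrival it slightly exceeds the stated ideal, so the wording should say what is acceptable. It should not rely on nurse transfer for cases, because the article offers that only when no hospital appointment is near.
- **Record timing at every visit.** For each urine sample, enter clock time and time since last food. At visit 4, also record whether it was passed before the fast, during it or after the meal.
- **Samples already collected.** Recover the timing where possible. Flag fasted and post-meal samples and examine them in a sensitivity analysis. Excluding them outright would remove mainly case samples at the only late time point and create missing data tied to case status.

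The conduct of the MMTT does not change. The cost is one home collection for some families and a few case report form fields. One limitation remains: an evening sample at week 52 may differ in time of day from weeks 0-8. Matching protects the case-sibling contrast at week 52, but the change within cases taken alone will still need the recorded times to interpret.
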